However, it is not yet clear how palliative care can be successfully integrated into COPD-care. At the moment, discussions on prognosis, goals of care and advance care planning rarely occur or only at a very late stage of the disease [9]. Neither are patients with COPD regularly referred to specialist palliative care [10]. As a consequence, patients with COPD are less likely to die at their preferred place of death, and symptoms remain undertreated [4, 11]. Previous research revealed three major barriers to palliative care provision in COPD [9, 12]. First, the unpredictable disease trajectory of COPD makes it difficult to determine when to start palliative care and discuss advance care planning. The second barrier is the lack of palliative care communication skills of professionals. The third barrier is related to a lack of care continuity and collaboration between healthcare professionals [12, 13].

In the COMPASSION (a central element in the provision of COPD-care [13] and acronym for COPD Palliative and Supportive care Implementation) study, we attempt to overcome these barriers towards the implementation of palliative care. In collaboration with patient and professional organizations, we developed an integrated palliative COPD care intervention that integrates existing scientific and practical knowledge. Moreover, to facilitate uptake of the intervention among healthcare professionals, a multifaceted implementation strategy was developed comprising a training, an online toolbox and support with planning and monitoring of implementation.

In this article, we will describe the aim, design and procedures of the COMPASSION study. Both the implementation process and clinical effectiveness of the integrated palliative care approach will be assessed. The COMPASSION study aims to:
investigate the effect of the implementation of integrated palliative care on patient, informal caregiver and healthcare professional outcomes;investigate the effect of the multifaceted implementation strategy on implementation outcomes and explore what barriers hamper the implementation of integrated palliative care in routine COPD-care;explore the relationship between implementation level and patient outcomes.

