### Intervention

Table 1 details the components of the integrated palliative care approach, consisting of an integrated palliative care intervention and an multifaceted implementation strategy. Figure 1 shows the causal assumptions of its outcomes and mechanisms of impact, based on the Medical Research Council framework [26]. The integrated palliative care intervention developed follows existing palliative care guidelines [27, 28], the Quality Framework Palliative care of the Netherlands [29], a literature review and input from the expert groups. For the identification of patients that are likely to benefit from palliative care, the previously validated Propal-COPD tool will be used. This tool has been validated in patients admitted to the hospital for acute exacerbation and showed to have a high sensitivity of 90% and specificity of 73% [16]. Moreover, admission for an acute exacerbation of COPD is considered to be one of the key milestones for transition towards a palliative approach [30] and seems to be a feasible moment to start proactive palliative care [31, 32]. After identification, one or more consultations take place either in the outpatient clinic or in the general practice, depending on the patient’s needs, for a multidimensional assessment, symptom management and advance care planning. The treatment plan and agreements made will be documented and shared with other involved professionals and discussed in a multidisciplinary meeting if needed. In case of preference for care at home, the responsibility will be transferred to the patient’s general practitioner. If a patient deceases, the provided end-of-life care will be evaluated with the patient’s informal caregiver and involved healthcare professionals.

**Table 1 Tab1:** Description of the implementation strategy and integrated palliative care intervention of the Compassion study

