### Implementation outcomes

*Context* refers to the larger physical, social, and political environment that either directly or indirectly affects the intervention. To study contextual characteristics of each intervention region, we will use field notes of training sessions, transcriptions of monitoring meetings, project meetings and interviews with implementation leaders and involved healthcare professionals.

*Reach* concerns the degree to which the intended audience participates in the intervention. Reach of the implementation strategy will be reported as the composition of the intervention teams, the absolute number and the proportion of professionals that participated in the training, using the attendance list of the training sessions. Reach of the intervention will be reported as numbers, proportions and characteristics of patients that received the integrated palliative care intervention.

*Dose delivered* is measured as the extent to which core elements of palliative care have been carried out by participating healthcare professionals, using questionnaires before and after the training. This measure reflects the effect of the implementation strategy on the care practices of each professional.

*Dose received* is measured as the extent to which core elements of palliative care are being received by participating patients, using patient questionnaires and medical chart review on received core elements.

*Fidelity* refers to the extent to which a patient was treated in accordance with the regional action plan. Fidelity checklists for each participating intervention patient will be filled out by the involved healthcare professional.

*Implementation* is a composite score indicating the extent to which the intervention has been implemented by professionals and received by patients. To compare the integrated palliative care provision between the intervention and control regions, the implementation score of delivered and received core elements of integrated palliative care will be calculated using the calculation method following Fleuren et al. [43].

*Recruitment* refers to the way we have recruited hospital regions to become involved in the implementation and evaluation of integrated palliative care in COPD.

*Maintenance* is the extent to which core elements of integrated palliative care is embedded in the routine organizational practices and policies.

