#### Analysis of process evaluation

All quantitative process data will be analyzed using descriptive statistics. We will examine the association between the implementation score and each effect outcome measure at patient level, using linear regression analysis. For this analysis, the dependent variable is the implementation score. Independent variables are patient outcomes at measurement point T6 or T12. Transcriptions of the semi-structured interviews, monitoring sessions and project meetings will be analyzed using inductively and deductively content analysis techniques supported by the qualitative analysis software Atlas.ti. Subsequently, triangulation of quantitative and qualitative results will take place.

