### Ethical considerations

The study has been approved by the Medical Ethics Committee (CMO) of the Radboud University Medical Centre (number 2018–4833). Since palliative care is additional to disease-oriented care, we do not expect any risks of participation for patients. The integrated palliative care intervention is patient-centred (adapted to the needs of every individual patient) and based on existing guidelines and thus could be considered as regular care. However, participation in this study will require filling out questionnaires which can be burdensome. To minimize the burden, we therefore limited the length and frequency of used questionnaires. Moreover, when selecting and writing questionnaires and information letters, we took into account that most patients are older and have a low education level.

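### The aim 3 regression of implementation score and outcome has no baseline or severity term, although care is adapted to need, so the association may be confounded by need

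*Protocol article*

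**What the plan says.** The third aim, at the end of the Background section, is to "explore the relationship between implementation level and patient outcomes". Analysis of process evaluation turns this into a patient-level regression: "We will examine the association between the implementation score and each effect outcome measure at patient level, using linear regression analysis". It names both sides of the model: "For this analysis, the dependent variable is the implementation score", and "Independent variables are patient outcomes at measurement point T6 or T12". No other term is listed.

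Under Implementation outcomes, the score "is a composite score indicating the extent to which the intervention has been implemented by professionals and received by patients". It therefore depends partly on what each patient received.

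Two sections tie that care to need. Ethical considerations states: "The integrated palliative care intervention is patient-centred (adapted to the needs of every individual patient". The Intervention section says that "one or more consultations take place either in the outpatient clinic or in the general practice, depending on the patient’s needs", and that the treatment plan goes to a multidisciplinary meeting only where this is required.

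The article's one sentence on covariate adjustment is in Analysis of effect evaluation. It concerns imbalance in baseline characteristics when the arms are compared.

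**The concern.** A patient's dose of palliative care is not randomised. Part of it is set by arm and part by how a region organises its care. By the protocol's own description, part may also follow the patient's needs. Need is also a plausible cause of poorer quality of life at 6 months. A regression that contains only the score and the follow-up outcome cannot separate the effect of more care from the reason for giving it.

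Adjusting for baseline imbalance between arms does not help. Arms can be perfectly balanced while, within each arm, patients with greater need receive more (or fewer) elements.

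At stake is the reading of aim 3. A flat or negative association could be taken to mean that better implementation brings no benefit, when it may partly show who was given the care. If need and dose are linked in the opposite direction, the association would look too favourable.

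**Working it through.** **1. Inputs from the documents.** The article gives no figure for the aim 3 regression. Sample size calculation gives SD 25, a relevant difference of 9 points, 121 per group, ICC 0.01, 10% loss and 347 patients in eight regions. These figures reproduce:

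- Per group: 2 × (1.96 + 0.84)² × 25² / 9² ≈ 121.
- Total: 242 × [1 + (30.25 - 1) × 0.01] / 0.9 = 347.5, with 242 / 8 = 30.25 per region.
- Analysed: 347 × 0.9 ≈ 312, or about 156 per arm.

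**2. Assumptions (not in the documents).** The correlation of dose with T0 quality of life is -0.2 to -0.3. The correlation of T0 with T6 quality of life is 0.5 to 0.6. Dose has no true effect and is related to T6 only through T0.

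**3. Spurious correlation.** r(dose, T6) = r(dose, T0) × r(T0, T6).

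- Low end: -0.2 × 0.5 = -0.10, which is -0.10 × 25 = -2.5 FACIT-Pal points per SD of dose.
- High end: -0.3 × 0.6 = -0.18, which is -0.18 × 25 = -4.5 points per SD of dose.

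**4. Chance of a false significant result, intervention arm only (n = 156).** By Fisher's z, power ≈ P(Z > 1.96 - atanh|r| × √(n - 3)), with √153 = 12.37.

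- r = -0.10: 0.1003 × 12.37 = 1.24, giving about 24%.
- r = -0.18: 0.1820 × 12.37 = 2.25, giving about 61%.

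A correlation is symmetric, so these figures do not depend on which variable is called dependent.

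**5. Both arms pooled (n = 312, √309 = 17.58).** The result depends on how far the arms differ in dose, because that randomised variation is unrelated to T0 and dilutes the correlation. An arm difference of d within-arm SDs divides r by √(1 + d²/4).

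- d = 1: r = -0.089 to -0.161, significant in about 35% to 82% of trials.
- d = 2: r = -0.071 to -0.127, significant in about 24% to 61%.

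**6. A true benefit with need omitted.** This was simulated with 39 evaluable patients per region and a true benefit of +3 points per unit of dose, the unit being the within-region SD. Outcome SD was 25 before the dose effect, dose was 1 SD higher in the intervention arm, and the region SD of dose was 0.3. All of these except the SD of 25 are assumptions. Here b is the correlation of need with within-region dose, and g is the points lost per SD of need. Mean unadjusted slopes:

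| g | b | Both arms | Intervention regions only |
|---|---|---|---|
| 10 | 0 | +3.1 | +3.1 |
| 10 | 0.3 | +0.7 | +0.3 |
| 10 | 0.5 | -0.8 | -1.7 |
| 15 | 0 | +3.0 | +3.0 |
| 15 | 0.3 | -0.4 | -1.2 |
| 15 | 0.5 | -2.7 | -4.0 |
| 20 | 0.2 | +0.1 | -0.8 |
| 20 | 0.3 | -1.5 | -2.5 |

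A closed form agrees: slope ≈ 3 - g × b / Var(dose). The pooled variance of dose is 1 + 0.3² + 0.25 = 1.34. For g = 15 and b = 0.3 this gives 3 - 4.5 / 1.34 = -0.4. With b = -0.3 it gives 3 + 4.5 / 1.34 = +6.4, so the direction of bias depends wholly on the sign of the need-dose link.

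Adjusting for need itself returned the slope to 2.9 to 3.1 in every scenario. In the trial, T0 variables are only markers of need, so recovery would be partial.

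**The case against.** **The need-dose link is inferred.** The scoring method comes from a cited source, and nothing shows that the score counts consultations. Most core elements in Table 1 are standard components, so the score may vary mainly with professional and regional uptake. The phrase about needs in the Intervention section may govern only where the consultation takes place, and adapted care can mean different content rather than more of it. This stands as a limit on size. It does not remove the concern, because the meeting held only where required and the statement in Ethical considerations remain.

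**The direction is not established.** A reader might infer that sicker patients receive more elements, so that the bias must run against the intervention. The documents do not show this. The sickest patients may receive fewer elements because they are readmitted, cannot attend or die early, and all analysed patients are already Propal-positive, which narrows the range of severity. The Background remark that advance care planning now happens rarely or late is suggestive for usual care, but says nothing about dose within this trial. This objection stands.

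**The size is assumed.** A reader might also carry the within-arm correlations unchanged to 312 pooled patients and obtain 42% to 89%. That ignores the dilution in step 5 and should not be quoted. Nor are points per SD of dose comparable like for like with the 9-point difference between groups.

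**The aim is exploratory, and covariates may be set elsewhere.** Aim 3 is worded as an association and makes no causal claim. An analysis plan that is not shown could add covariates. However, the article does not leave the model open: it names the variables on both sides, and as stated the model is unadjusted.

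**Conclusion.** The concern holds as possible confounding by need in an exploratory analysis. The stated model has no baseline outcome, severity, arm or region term, while the same article says that care is adapted to each patient. The documents fix neither the direction nor the size of any bias.

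If sicker patients receive more elements, a beneficial relationship is attenuated, and with a stronger link it can reverse. Under the assumed correlations, a spurious correlation of -0.10 to -0.18 would be significant in about 24% to 61% of trials with 156 intervention patients. With a weak link the effect is only mild attenuation. The randomised comparison of the primary outcome is untouched.

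**What to change.** In the aim 3 model:

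- Add the T0 value of the same outcome where Table 2 schedules one, the Propal-COPD score (calculated in both arms) and the baseline severity items already collected: long-term oxygen, home non-invasive ventilation, previous ICU admission, previous mechanical ventilation and opioid use.
- Account for arm (fixed term) and region (random effect), in line with the multilevel models planned for the effect evaluation. These terms alone are not enough, since the within-region association that remains is where individual need acts.
- Report the result as an adjusted, non-causal association, and state that need arising after T0 remains uncontrolled.

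A plot of the eight region-mean implementation scores against region-mean baseline-adjusted outcomes is optional. It should be descriptive and shown by arm, because otherwise much of its spread may simply restate the randomised contrast.

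The cost is a change of analysis wording and slightly more analysis work. No new data are needed.

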### Effect evaluation

An overview of the data collection process, detailing the timing of data collection and the outcome measures and instruments used, is provided in Table 2.

**Table 2 Tab2:** Data collection schedule and measurement instruments for patients, informal caregivers and healthcare professionals

	Measurement instrument				
**Patient**		**T0**	**T3**	**T6**	**R**
Baseline characteristics	Questionnaire on demographic characteristics and case report form on disease severity	x			
Quality of life (primary outcome)	Functional Assessment of Chronic Illness Therapy-Palliative care (FACIT-Pal) scale [35]	x	x	x	
Spiritual well-being	Functional Assessment of Chronic Illness Therapy - Spiritual Well-Being (FACIT-Sp-12) scale [36]	x	x	x	
Anxiety and depression	Hospital Anxiety and Depression Scale (HADS) [37]	x	x	x	
Disease-specific health-related quality of life	Clinical COPD Questionnaire (CCQ)	x	x	x	
Satisfaction with care	Single item question on satisfaction with provided care, self-rated on a numeric rating scale (NRS) from 0 to 10	x		x	
Unplanned healthcare use	Medical record assessment on number of ED visits (without admission), hospital admission (number and number of days), ICU admission (number and number of days), in the 12 months pre-enrollment up to 12 months after enrollment				x
Date and place of death, place of care in last week of life if applicable	Medical record assessment (and contact with general practitioner if needed)				x
Dose received	Questionnaire on received core elements, based on three validated questionnaires [38–40]	x		x	
	Medical record assessment on core elements				x
Experiences and acceptability	Semi-structured interviews		x^a^		
**Informal caregiver**		**T0**	**T3**	**T6**	
Baseline characteristics	Questionnaire on demographic characteristics	x			
Caregiver burden	Caregiver Reaction Assessment (CRA) scale [41]	x	x	x	
Satisfaction with care	Single item question on satisfaction with provided care to the patient, self-rated on a NRS from 0 to 10	x		x	
Experiences and acceptability	Semi-structured interviews		x^a^		
**Health care professional**		**iT0**	**iT3**	**iT12**	
Self-efficacy	End-of-life professional caregiver survey (EPCS) [42]	x	x	x	
Role identity	Developed five-item question on role identity based on MIDI questionnaire [43]	x	x	x	
Satisfaction with care	Single item question on satisfaction with provided palliative care to patients with COPD, self-rated on a 5-point Likert scale	x	x	x	

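### The aim-3 implementation score and the outcomes it is related to come from the same follow-up, so care with no effect can still appear associated with healthcare use and survival

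*Protocol article*

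**What the plan says.** The third aim in the Background is to "explore the relationship between implementation level and patient outcomes". The section Analysis of process evaluation carries it out: "We will examine the association between the implementation score and each effect outcome measure at patient level, using linear regression analysis". It adds: "For this analysis, the dependent variable is the implementation score". It then says: "Independent variables are patient outcomes at measurement point T6 or T12".

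Under Implementation outcomes, the score is a composite of what professionals implemented and what patients received. The received part, dose received, is measured "using patient questionnaires and medical chart review on received core elements". Table 2 gives the patient questionnaire at T0 and T6 only. It lists the chart part as "Medical record assessment on core elements", marked retrospective, with no start or end date. The professional part (dose delivered) is collected at iT0, iT3 and iT12.

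The effect outcomes include unplanned healthcare use, counted "in the 12 months pre-enrollment up to 12 months after enrollment", and date and place of death. Table 2 has no T12 column for patients, so I read T12 as these 12-month record data. Table 1 lists dying-phase and bereavement care among the components of the intervention. The Intervention section says that "admission for an acute exacerbation of COPD is considered to be one of the key milestones for transition towards a palliative approach". Patients are included on a positive Propal-COPD score, which the Patients section describes as marking a high probability of death within a year.

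**The concern.** An analysis of whether more implementation goes with better outcomes needs an exposure that is settled before the outcome is counted. Here the patient-level exposure is collected over the follow-up in which the outcomes occur. Three mechanisms follow.

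- **Time alive.** Most core elements can be received only while the patient lives, so early death caps the score.
- **Readmission.** An admission is an occasion to deliver and record core elements, so the outcome can generate the exposure.
- **Dying phase.** These elements can be scored only for patients who die, which pushes the survival association the other way.

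The T6 questionnaire outcomes have a narrower problem. The received-care questionnaire is completed at the same time point by the same patient, and chart elements prompted by readmission also enter the score.

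Making the outcome the dependent variable, adjusting for baseline severity or modelling region would not separate the two windows. At stake is the answer to aim 3: care that does nothing could appear related to admissions or survival.

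**Working it through.** **Inputs from the article.** 347 patients (Sample size calculation); one-year mortality after admission up to 23% (Background); Propal-COPD sensitivity 90% and specificity 73% (Intervention). The article gives no figure for aim 3 to reproduce. The 347 serves only as the number of simulated patients.

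**Mortality range.** Applying the tool's accuracy to 23% prevalence (an assumption) gives one-year mortality among positives of 0.9×0.23 / (0.9×0.23 + 0.27×0.77) = 0.207/0.4149 = 0.50. I therefore take 23% to 50% as the range. With constant hazard, deaths by month 3 are 1 − 0.77^0.25 = 6% to 1 − 0.50^0.25 = 16%.

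**Mechanism by hand.** Assume that each element has a 5% chance per month alive and an extra chance q per readmission, with no effect on any outcome. The expected score out of 100 is 100 × [1 − 0.95^months × (1 − q)^readmissions].

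- Death at month 2, no readmission: 1 − 0.95^2 = 0.0975, about 10 points.
- Alive at month 12, no readmission: 1 − 0.95^12 = 0.46, about 46 points.
- Alive at month 12, two readmissions, q = 0.3: 1 − 0.54 × 0.49 = 0.735, about 74 points.

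**Null simulation A.** Six elements under the formula above, one-year mortality 23% or 40%, 0.5 to 1.5 admissions a year, 500 runs per scenario, score and outcomes over the same 12 months.

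| Setting | Correlation of score with admissions | Significant | Survivors minus decedents |
|---|---|---|---|
| q = 0 | 0.09 to 0.24 | 40–100% of runs | 21 to 23 points |
| q = 0.15 or 0.30 | 0.31 to 0.65 | 100% | 23 to 30 points |

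The survivor difference was significant in every run.

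**Null simulation B, varying delivery time.** Four elements, mortality 23% to 50%, 1.5 admissions a year, readmission given no role in delivery.

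- Mean 6 months to each element: correlation with survival time 0.68 to 0.76; with admissions 0.22 to 0.34 (significant in 99–100% of runs).
- Early delivery (60% of patients ever receive elements, mean 1.5 months in intervention regions, rare in control): survival 0.13 to 0.19 (75–96%); admissions 0.04 to 0.08 (12–38%).
- Score limited to the first 6 months, outcomes to 12 months: still falsely significant in 34–100% of runs for survival and 8–73% for admissions.

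**Adding a dying-phase element.** With elements delivered at a mean of 1 to 1.5 months and the dying-phase element recorded in 90% of deaths, a survival correlation of up to about 0.66 falls to between −0.13 and 0.23. In another early-delivery case it moves from 0.21 to −0.09. The sign can reverse.

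**Testing the remedy.** In simulation A, I fixed the score at 3 months and counted only later outcomes in patients alive then. Correlation with admissions is −0.004 to 0.004, the score difference is within 0.2 points, and false significance is 3–8%. That model gives all patients the same admission rate. If rates differ between patients and admissions trigger care, the landmark alone leaves 31–82% false significance for later admissions. Adjusting for admissions before enrolment and in the first 3 months brings it to about 2–8%.

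**The case against.** The case on the other side is substantial, and several parts of it stand.

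- **The chart window.** A reader might infer that the chart review is open-ended. The article only leaves the window unstated, and an article commonly leaves such detail to the full protocol. The full-period figures therefore show what could happen, not what is planned. A 6-month window would not cure the problem, however, and the T6 timing of the questionnaire is fixed in Table 2.
- **Direction.** A reader might infer that patients who live longer must score higher. Table 1 does not support that, because dying-phase and bereavement elements can be recorded only for patients who die.
- **Score construction.** The composite follows a cited method not shown here, and it includes a professional component that does not depend on any one patient's survival. This dilutes the artefact but does not remove it.
- **Delivery timing.** The Intervention section places consultations after identification, so early delivery fits better than a 6-month mean. The smaller correlations are then the more relevant ones for survival and, if readmissions prompt nothing, for admissions.
- **FACIT-Pal and the other T6 questionnaires.** A reader might infer that immortal time distorts these too. It cannot, because everyone who answers at T6 has survived to T6. A T6 report of care also looks back, so part of the exposure precedes the T6 state.
- **Importance.** Aim 3 is worded as exploratory and as an association. The Discussion ties scale-up to the approach being proven effective, not to aim 3.

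None of this separates the exposure window from the outcome window for healthcare use and death.

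**Conclusion.** The point holds for the aim-3 association with unplanned healthcare use and with survival. As written, the analysis can return a clear association when care has no effect. For admissions the spurious correlation runs from 0.04 to 0.34 if readmissions prompt no care and from 0.31 to 0.65 if they do. For survival it can be strong, weak or reversed, depending on how quickly elements are delivered and whether dying-phase care is scored.

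These sizes depend on assumed delivery times, admission rates, chances of readmission prompting care, and mortality above the 23% in the article. They also model the patient-level part of the score alone, so the composite would show less. For the T6 questionnaires the concern is limited to same-time measurement and readmission-driven scoring, and no size was computed. The randomized comparison and the primary outcome are not affected.

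**What to change.** In Analysis of process evaluation, separate the two windows for the aim-3 association:

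1. Record the date of each core element during the chart review already planned.
2. Build the patient score only from elements dated within a fixed early window, for example 3 months from inclusion, leaving out dying-phase and bereavement elements.
3. Include patients alive at the end of that window.
4. Relate the score only to later outcomes: questionnaires at T6, and healthcare use and survival from month 3 to month 12.
5. Adjust for admissions before enrolment and within the window. Both come from the healthcare-use record already planned. A landmark alone does not deal with patients who are simply prone to admission.
6. Keep the T6 and full-period score for describing dose received and comparing it between arms.

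The cost is the dating of elements and some precision. Deaths before month 3 (about 6% to 16% under a constant hazard) and elements delivered later leave this exploratory model. No extra patients, visits or T3 questionnaire are needed.

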**Fig. 3 Fig3:**
[figure not shown]
Flowchart of procedures with timelines of (**a**) healthcare professionals and (**b**) patients and informal caregivers. Abbreviations HCP: health care professionals; iT0: professional timeline at baseline (pre-implementation); iT3: 3 months after inclusion of first included patient (initial implementation); iT12: 12 months after training (intervention regions) or inclusion of first patient (control regions) (late implementation); T0: patient timeline at baseline; T3: patient timeline at 3 months; T6: patient timeline at 6 months; R: retrospectively

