### Analysis

#### Analysis of effect evaluation

Data cleaning and all analyses will be carried out using statistical software that supports multilevel mixed model analyses, such as IMB SPSS Statistics 25. Baseline characteristics of region and study population will be analyzed using descriptive statistics. Continuous variables will be reported as mean and standard deviation and categorical variables as frequency or percentage. The statistical analyses will be done by an intention-to-treat approach. All analysis will be considered significant if α < 0.05. We will analyze differences between the control and the intervention group for the primary and secondary outcomes on the patient, informal caregiver and professional level using multilevel mixed model analyses that will account for the clustered study design (i.e. patients and professionals nested within a region). We will check for eventual unbalances in baseline characteristics and adjust for these variables if needed.

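### The regression for the third aim has exposure and outcome the wrong way round and cites a patient time point, T12, that the data schedule does not define

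*Protocol article*

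**What the plan says.** The third aim, at the end of Background, is to "explore the relationship between implementation level and patient outcomes". The only quantitative analysis described for it is in Analysis of process evaluation: "We will examine the association between the implementation score and each effect outcome measure at patient level, using linear regression analysis". The roles are then fixed: "For this analysis, the dependent variable is the implementation score. Independent variables are patient outcomes at measurement point T6 or T12".

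Under Implementation outcomes, the score "is a composite score indicating the extent to which the intervention has been implemented by professionals and received by patients". The legend of Fig. 3 lists the patient time points as baseline and 3 months, then "T6: patient timeline at 6 months; R: retrospectively". For the effect evaluation, the preceding section commits to multilevel mixed models that "account for the clustered study design (i.e. patients and professionals nested within a region". The process section names only linear regression.

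**The concern.** The article treats implementation as the driver and patient outcomes as the response. Its Intervention section presents a model of causal assumptions and expects the core elements to produce the effect, and the score measures how far those elements were delivered and received. The regression reverses this. Its coefficient is units of implementation score per point of outcome, whereas a reader of the third aim wants the difference in outcome, for example in FACIT-Pal points, that goes with a higher score.

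The time point is a separate fault. An analyst told to use T6 or T12 finds no T12 for any patient measure and is not told which outcome belongs to which point.

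At stake is an interpretable effect size for one of three stated aims, and an analysis that two analysts would run in the same way.

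**Working it through.** The plan states no figure for this analysis, so there is none to reproduce. Three checks follow.

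**1. Direction.** Let x be the implementation score, y one patient outcome and r their correlation.

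- Slope of interest: b(y on x) = r × SD(y)/SD(x).
- Slope as specified: b(x on y) = r × SD(x)/SD(y).
- Their product is r². Both have the test statistic t = r × √((n − 2)/(1 − r²)), and so the same p-value.

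On one simulated dataset with n = 312 the slopes were 0.2503 and 0.2345. Their product is 0.0587, equal to R². The p-value was 1.5e-05 in both directions, and the two p-values also agreed with a shared covariate in both models. For one outcome in an ordinary linear regression, reversal changes the slope and its meaning but not the test.

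This fails once several outcomes enter one model, which the plural wording on independent variables permits. Take two standardised outcomes that each correlate r with the score and ρ with each other. Each coefficient is r(1 − ρ)/(1 − ρ²) = r/(1 + ρ), which falls from r towards r/2 as ρ goes from 0 to 1. Each outcome is then judged conditional on the other, which is not the association of interest.

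**2. Time point.** The relevant places side by side:

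| Place | Content |
|---|---|
| Procedures | Patient follow-up questionnaires at 3 and 6 months only |
| Fig. 3 legend | Patient points T0, T3, T6 and R |
| Table 2 | FACIT-Pal, FACIT-Sp-12, HADS and CCQ at T0, T3, T6 |
| Table 2 | Unplanned healthcare use from records up to 12 months after enrolment, under R |
| Table 2 | Date and place of death under R, no window given |
| Fig. 3 legend, Table 2 footnote | iT12, on the professionals' timeline |
| Analysis of process evaluation | Patient outcomes at T6 or T12 |

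If T12 means iT12, it is not a patient measurement. If it means the 12-month record data, it carries the wrong label and fits only one outcome with a stated window, while the sentence covers every patient-level outcome. Either way the text needs correcting.

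**3. Clustering, sized only for the case that region is left out.** Inputs: 347 patients, 10% loss, eight regions and ICC 0.01 (Sample size calculation). Analysed patients: 347 × 0.9 = 312.3, so 312, or 39 per region. The variance of an unclustered slope is inflated by 1 + (39 − 1) × ICC(score) × ICC(outcome). The ICC of the score is not given, so its full range is shown. Type I error at nominal 0.05 comes from 20,000 null simulations per row.

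| ICC of score (assumed) | Inflation, outcome ICC 0.01 | Type I error |
|---|---|---|
| 0 | 1.00 | 0.053 |
| 0.1 | 1.038 | 0.053 |
| 0.3 | 1.114 | 0.060 |
| 0.5 | 1.19 | 0.066 |
| 1.0 (purely regional) | 1.38 | 0.097 |

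If the outcome ICC were 0.05, which is an assumption and not in the article, the type I error would run from 0.052 to 0.247 over the same rows.

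**The case against.** The strongest defence is that the third aim is exploratory and states no direction, and the analysis sentence speaks only of association. As check 1 shows, a one-outcome reversed model gives the same test. That stands: a reader might infer that the planned regression cannot answer the third aim, and the article does not support so strong a claim.

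T12 may also be no more than a mislabel for the 12-month healthcare-use records, so it would be wrong to infer that no 12-month patient data exist. That too stands, but the label still needs correcting.

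A reader might further infer that clustering is ignored and that arm and baseline are left out. The section neither includes nor excludes them. The phrase about patient level may only say which outcomes are meant, and a condensed article may leave the full model to the analysis plan. These are silences and not errors. The patient-received part of the score also argues against treating it as purely regional, which is the only case in which the type I error approaches 0.10 at the stated ICC.

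Finally, dose received is taken from questionnaires at T0 and T6 and from later record review, so part of the score is measured at the same time as the T6 outcome or after it. Swapping the variables therefore does not by itself license a causal reading. None of this rescues the two explicit statements, the assigned roles and T12.

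**Conclusion.** The point holds in two parts, both resting on stated text. The assigned roles are reversed, so the slope does not estimate how patient outcomes vary with implementation level. T12 is not a defined patient measurement point.

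The loss is an interpretable effect size and a clear choice of time point. The test of association survives if each model holds a single outcome, and not otherwise. It would be tempting to quantify the reversal by inverting the slope, or to call the result badly over-precise. The first needs a step that the article does not plan and a correlation that it does not give. The second needs a higher outcome ICC or a largely regional score.

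At the article's ICC of 0.01, leaving out region would give a type I error of about 0.05 to 0.10, depending on the unknown ICC of the score. The severity is moderate: this is an exploratory secondary aim, and the primary outcome, the sample size and the effect models are not affected.

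**What to change.** Rewrite the two sentences in Analysis of process evaluation along these lines:

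- Each patient outcome is the dependent variable and the implementation score is the independent variable, with one model per outcome.
- Questionnaire outcomes are taken at T6. Unplanned healthcare use is taken over the 12-month record window. The label T12 is removed.
- The model uses the region-level multilevel structure already specified for the effect evaluation in place of plain linear regression, with the T0 value of the outcome as a covariate where it is collected.

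The cost is two or three sentences. No new data, visits or patients are needed, and the primary analysis does not change.
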